**Methods:**

Systemic organ communication in STEMI (SYSTEMI) is an all-comer open-end prospective study in STEMI patients > 18 years of age to assess the interaction of cardiac and systemic metabolism in STEMI by systematically collecting data on a regional and systemic level. Primary endpoint will be myocardial function, left ventricular remodelling, myocardial texture and coronary patency at 6 month after STEMI. Secondary endpoint will be all-cause death, MACCE, and re-hospitalisation due to heart failure or revascularisation assessed 12 month after STEMI. The objective of SYSTEMI is to identify metabolic systemic and myocardial master switches that determine primary and secondary endpoints. In SYSTEMI 150–200 patients are expected to be recruited per year. Patient data will be collected at the index event, within 24 h, 5 days as well as 6 and 12 months after STEMI. Data acquisition will be performed in multilayer approaches. Myocardial function will be assessed by using serial cardiac imaging with cineventriculography, echocardiography and cardiovascular magnetic resonance. Myocardial metabolism will be analysed by multi-nuclei magnetic resonance spectroscopy. Systemic metabolism will be approached by serial liquid biopsies and analysed with respect to glucose and lipid metabolism as well as oxygen transport. In summary, SYSTEMI enables a comprehensive data analysis on the levels of organ structure and function alongside hemodynamic, genomic and transcriptomic information to assess cardiac and systemic metabolism.

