## Methods/Design

### Design, setting and endpoints of the study

SYSTEMI is an investigator-initiated, open-end prospective, observational, multicentric, cohort study of all-comer patients with STEMI supported by the German Research Council (CRC 1116, Grant No. 236,177,352). Ethics approval was given by the local ethics committees (Heinrich-Heine-University, Düsseldorf, Germany; and Landesärztekammer Nordrhein) complying with the Declaration of Helsinki under reference numbers 5961R and 2,021,055. SYSTEMI is registered at www.clinicaltrials.gov: NCT03539133. SYSTEMI will recruit patients at the academic main-hospital of Heinrich Heine University Düsseldorf, Germany with > 150 STEMI per year, as well as in secondary pPCI -centres within the academic network of Heinrich Heine University Düsseldorf (“Heart-net”), Germany with > 80 STEMI per year. To optimize recruitment efficacy, training sessions have been performed with the interventional staff on call and the study nurses to best inform the patients about the study dependent examinations during their guideline directed diagnostics and therapy at index hospitalisation. As shown in the study flow (Fig. 1A), data will be collected at the index hospitalization (index event within the catheter laboratory + 1–5 days), as well as at follow-up (FU) visits at 6 and 12 months after STEMI at each of the recruiting centers. Follow up phone calls will be performed annually for up to five years. As shown in Fig. 1B, the primary endpoints are imaging-derived LV ejection fraction (LVEF), indexed LV stoke volume (SVi), increase in LV indexed end-diastolic volume (LVEDVi) and LV texture (T1, T2, ECV) using either 3-dimensional echocardiography or CMR 6 months after STEMI as well as angiography derived coronary patency rate at 6 month after STEMI. Secondary endpoint is a composite of all cause mortality, MACCEs (cardiovascular death, nonfatal stroke or myocardial infarction) and rehospitalization due to heart failure within 12 months after STEMI.

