Within the first and third day after reperfusion we will conduct additional cardiac imaging with transthoracic echocardiography and in a subset of patients cardiovascular magnetic resonance (CMR) (1.5 & 3.0T Achieva, PHILIPS Healthcare, Best, Netherlands) including measurements of ventricular mass, volume, function and myocardial relaxometry (V2 + V4). Cine imaging will be used to calculate pressure-volume curves by taking phase-to-phase volumes of short-axis slices, blood pressure and left ventricular end-diastolic pressure measurements from acute catheterization measurements [17]. Additionally, native relaxometric mapping of the myocardium (T1, T2, T2*) [18], gadolinium contrast-enhanced imaging and postcontrast relaxometric mapping (T1, extracellular volume fraction, ECV) will be performed to assess the myocardial inflammation/edema extent, extracellular volume, fibrosis and iron content. For this, validated sequences will be used as outlined in Additional File Table 1. Gadolinium-enhanced images will be used to assess markers of infarcted tissue, such as edema, infarct size (IS), microvascular obstruction (MVO), and intramyocardial hemorrhage (IMH). Certified CMR evaluation software will be used for all analyses (CVI42, Circle Cardiovascular Imaging Inc., Calgary, Alberta, Canada or Sectra Workstation IDS7, Version 19.3.6.3510). This will be accompanied by an additional liquid biopsy. These early measurements after reperfusion will give insight in very early adaptations in ventricular volume and dimensions, which will serve to associate ventricular volume and dimension with systemic blood derived markers. Blood samples will also be collected to assess arterial or venous lactate, hemoglobin A1c (HbA1c), fasting blood glucose and insulin for calculating the Homeostasis Model Assessment indices (HOMA-IR and HOMA-B). Additionally, a detailed assessment of anemia will be performed, including parameters of RBC turnover, formation, (dys)function, and hemolysis. Specifically, we will address absolute and relative iron deficiency (ID), one of the most common reasons of anemia, especially in elderly patients with comorbidities, by measuring free iron, ferritin, transferrin, the soluble transferrin receptor and transferrin saturation in the collected blood samples. This will be done during V2.

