### Statistical approach

SYSTEMI was designed as open-end prospective cohort study in all comer STEMI patients. No formal sample size calculation has been performed. It was anticipated that more than 160 STEMI patients per year will be a realistic recruitment speed on the basis of expected STEMI patients at host institutions to reach a total sample size of > 1000 STEMI patients.

This cohort study was designed to unravel novel master switches and markers of metabolic networks in STEMI patients to further facilitate risk stratification and identify novel therapeutic targets in STEMI. For primary endpoints, logistic regression analysis will be used to model the predefined outcome data with impact of covariates. The effects of the independent parameters in these regression models will be estimated (odds ratio, hazard ratio) and presented with 95% confidence intervals. Network analysis using machine learning approaches for unsupervised metabolic cluster identification will be conducted. Secondary endpoint analysis will be performed using Kaplan–Meier plots and the log-rank test. Two-tailed p values below 0.05 will be considered indicative of statistically significant differences. Since significant interactions of master switches within the metabolic network are anticipated, interim analysis will be done after 500 and 1000 patients for a robust statistical power calculation and re-adjustment of investigations.

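### The only test named for the 12-month secondary endpoint compares groups, so any continuous candidate master switch tested this way would have to be categorised, at a cost in power

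*Protocol article*

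**What the plan says.** The Statistical approach section treats the two endpoint families differently. For the primary endpoints it states logistic regression with covariates, and says that effects in those models will be reported as odds ratios and hazard ratios with 95% confidence intervals. For the 12-month composite it states: "Secondary endpoint analysis will be performed using Kaplan–Meier plots and the log-rank test". It names no regression model for that endpoint. Significance is set by a single rule: "Two-tailed p values below 0.05 will be considered indicative of statistically significant differences". On size, it says "No formal sample size calculation has been performed" and gives an aim "to reach a total sample size of > 1000 STEMI patients".

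The abstract sets an objective that covers both endpoint families: "The objective of SYSTEMI is to identify metabolic systemic and myocardial master switches that determine primary and secondary endpoints". The secondary endpoint combines all-cause mortality, MACCE and "rehospitalization due to heart failure within 12 months after STEMI".

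The Study processes and protocols section lists what is measured. Continuous quantities include HbA1c, "fasting blood glucose and insulin for calculating the Homeostasis Model Assessment indices (HOMA-IR and HOMA-B"), and the spectroscopy readings of fatty acids, total creatine, ATP, inorganic phosphate and pH. The same section lists "free iron, ferritin, transferrin, the soluble transferrin receptor and transferrin saturation", which are collected to assess iron deficiency. It also describes variables that are groups by nature: diabetes endotype and glucose-tolerance class. Unsupervised metabolic clusters appear in the aims and in the Statistical approach section.

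**The concern.** Kaplan–Meier curves and the log-rank test need defined groups. A continuous marker can enter them only after it has been cut into categories. The study searches for markers, and its stated objective extends to the secondary endpoint, so the stated test does not fit some of the candidates.

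Two things are at stake. First, categorising a continuous marker discards information, so real associations with the 12-month composite are more likely to be missed. Second, a cut chosen after looking at the curves makes the stated 0.05 threshold too lenient, and false switches may be reported. Adjusting or stratifying the log-rank test for covariates removes neither problem, because the marker would still have to be cut.

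**Working it through.** The article gives no power, event count or effect size, so there is no figure of its own to reproduce. What follows shows the size of the effect under assumptions.

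**From the article:** two-sided alpha 0.05; more than 1000 patients intended (1000 used); 12-month endpoint; log-rank as the test.

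**Assumed:** a normally distributed marker; log hazard linear in the marker; proportional hazards; 10–15% of patients with an event by 12 months (100–150 events); hazard ratio 1.2 or 1.3 per SD.

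**1. Information kept by a two-group cut.** With the cut at c and a proportion p below it, the fraction kept is φ(c)²/[p(1−p)].

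- Median: 0.3989²/0.25 = 0.637 = 2/π, a loss of 36%. This is the smallest loss any two-group cut can give for a normal marker.
- 75th percentile: 0.539 kept, a loss of 46%.
- 90th percentile: 0.1755²/0.09 = 0.342 kept, a loss of 66%.

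For more than two groups, scored by their means, the fraction kept is the sum of p_k × (group mean)². Losses are 21% for tertiles, 14% for quartiles and 10% for quintiles. These figures presume a trend-type test. An ordinary log-rank test across five groups spends four degrees of freedom, and so has less power against a monotone effect than the 10% suggests.

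**2. Power.** For the continuous marker, z = ln(HR) × √events. For a median split, multiply z by √(2/π) = 0.798. Power = Φ(z − 1.96).

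| HR per SD | Events | z, continuous | Power | z, median split | Power |
|---|---|---|---|---|---|
| 1.3 | 150 | 0.2624 × 12.25 = 3.21 | 90% | 2.56 | 73% |
| 1.3 | 100 | 0.2624 × 10 = 2.62 | 75% | 2.09 | 55% |
| 1.2 | 150 | 0.1823 × 12.25 = 2.23 | 61% | 1.78 | 43% |
| 1.2 | 100 | 0.1823 × 10 = 1.82 | 45% | 1.45 | 31% |

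A simulation of 4000 data sets (1000 patients, 12% events, HR 1.3 per SD) gave 83% against 63%. The formula gives 82% against 63%.

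**3. Events for 80% power at HR 1.3 per SD.** Continuous: (1.96 + 0.842)²/0.2624² = 114.0, so 115. Median split: the log hazard ratio between halves is 2 × 0.798 × 0.2624 = 0.419, and 4 × 7.85/0.419² = 179.1, so 180. The ratio is 180/115 = 1.57, about π/2.

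**4. If the cut were chosen from the data.** With no true effect and 1000 patients, taking the most significant of 17 cuts between the 10th and 90th percentiles gave p < 0.05 in 28.9% of simulations at 10% events and 30.5% at 15%. At 12% events, searching every cut gave about 35% over the 20th–80th percentiles and 44% over the 10th–90th. A fixed median cut held its level at 5.2%.

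**The case against.** The strongest reply is that the article never says a continuous marker will be split. The sentence just before the log-rank sentence announces unsupervised cluster identification, and the Conclusion speaks of endotypes of diabetes and anemia. Those are groups, and the log-rank test suits them. Some continuous readings also feed a stated clinical class: the iron indices serve iron deficiency, and lactate serves cardiogenic shock. All of this stands. A reader might infer that the plan forces every switch to be dichotomised, that a third of the information is lost throughout, or that cut-points will be searched for. The document supports none of these.

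A second reply is that the hazard ratio in the Statistical approach section shows that a Cox model is intended. It may be. Logistic regression yields no hazard ratio, and the only time-to-event analysis described is the secondary one. But the wording attaches the hazard ratio to the regression models for the primary endpoints, and no Cox model is named, so the mention does not settle the matter.

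A third reply is that a journal article may leave group definitions to the full protocol or analysis plan, which are not shown. That is right, and missing cut-points are not the complaint here. The point concerns the method that the article does state, and its fit to an objective that includes continuous candidates.

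Finally, this is a secondary endpoint in an exploratory cohort without a sample size calculation. That limits the weight of the point but does not remove it.

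**Conclusion.** The point holds conditionally. As written, the only test named for the 12-month composite compares groups. It is appropriate for clusters, endotypes, IFG/IGT/T2DM status and iron deficiency. It is a poor choice for candidates such as HOMA-IR, HOMA-B, HbA1c and the spectroscopy metabolites if these are tested singly.

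For those, the loss depends on the grouping: 36% of the information at a median split, about 10% with quintiles under a trend-type test, and about 66% with a cut at the 90th percentile. At HR 1.3 per SD, with 1000 patients and 10–15% events, a median split lowers power from 75–90% to 55–73%. Event rates, effect sizes, normality and linearity are assumptions, not figures from the article. Over a wider assumed range (8–20% events, HR 1.2–1.4 per SD, 1000 patients) a median split costs about 3 to 19 power points.

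The false-positive rates of roughly 29–44% apply only if cuts are chosen from the data. They show what an unfixed cut would permit and do not describe a stated intention.

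**What to change.** In the Statistical approach section, state three things:

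- Continuous master switches are tested against the secondary endpoint by Cox regression with the marker kept continuous, on the log scale or as a spline with fixed knots. This model is the source of the hazard ratio.
- The log-rank test is kept for variables that are groups by nature or are specified in advance, such as clusters, endotypes, IFG/IGT/T2DM status and iron deficiency.
- Kaplan–Meier curves for continuous markers are drawn at fixed quantiles, for display only and without a test.

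The change takes a few lines of text and alters no data collection. The added work is checking proportional hazards and the functional form of each marker.

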## Discussion

Mortality and morbidity after STEMI remain high and current risk prediction models do not take metabolic risk constellations into account. Therefore, the overall objective of SYSTEMI is to identify systemic and myocardial metabolic master switches that determine outcomes after STEMI. To reach this objective, we have designed and set-up SYSTEMI to comprehensively investigate systemic and myocardial metabolism at index hospitalization and at 6 months in more than 1000 patients. SYSTEMI will enable in-depth analyses of systemic metabolic effectors on local myocardial function and metabolism, as detected by magnetic resonance imaging and spectroscopy, and clinical outcome.

### SYSTEMI metabolic clusters

To our knowledge, the present cohort study is the first study in patients with STEMI to systematically and simultaneously assess organ-function, inter-organ communication as well as myocardial and systemic metabolism. SYSTEMI focuses on 3 metabolic clusters: (i) the glucometabolic spectrum, (ii) the lipid metabolism and (iii) the O_2_ transport capacity of the blood. The first metabolic cluster covers the glucometabolic spectrum of hyperglycemia, hyperinsulinemia, and insulin resistance to T2DM and the role of specific endotypes of T2DM in patients with STEMI. Altered glucose metabolism can be seen in up to 50% of all STEMI patients, but only 25% remain in this state after 3 months [20]. Moreover, the hyperglycemic status of diabetic and nondiabetic patients has been shown to influence IS, MVO and LVEF post-STEMI [20]. Therefore, SYSTEMI will focus on glucometabolic phenotyping using various methods, including OGTT, homeostatic model assessment, or endotyping of T2DM. Endotyping of T2DM has shown different prevalence rates of diabetes-related complications, although their impact on STEMI patients remains unknown [13, 14]. In this context, the severe insulin-resistant diabetes (SIRD) endotype may specifically predispose STEMI patients to metabolic and myocardial alterations. SIRD has been associated with elevated levels of biomarkers of inflammation and a higher risk of diabetic kidney disease [13, 14]. This characterization may help to guide targeted therapeutic regimens for patients with STEMI and T2DM. The recent introduction of sodium-glucose cotransporter-2 inhibitors into guidelines for heart failure in patients with and without T2DM has highlighted the importance of glucometabolic modulation in cardiovascular disease to improve patient outcomes [21]. The second metabolic cluster covers the crosstalk of cardiac ischemia with changes in lipid metabolism in the presence and absence of alterations of the glucometabolic spectrum. The impacts of browning adipose tissue [22], the lipolytic response in skeletal muscle, and circulating lipoproteins, ceramides, and the HDL sphingolipidome [23] on infarct will be investigated. The third metabolic cluster covers function and dysfunction of red blood cells in anemia [24]. Anemia affects systemic energy metabolism through multiple mechanisms, including limited oxygen transport capacity, disturbed iron metabolism, and altered hepatic metabolism, and is associated with profound red blood cell (RBC) dysfunction [24]. This appears to be an important modulator of interorgan crosstalk after STEMI. The prognosis of STEMI is limited by anemia and secondary complications such as bleeding, thrombosis, inflammation, and arrhythmia [25].

### SYSTEMI approaches to characterize myocardial and systemic metabolism

To enable comprehensive investigation of the bidirectional interaction of systemic and cardiac metabolism through the aforementioned pathways in the acute phase of STEMI and its long-term outcome in patients, several layers of analysis have to be accomplished within SYSTEMI: (i) analysis of cardiac and circulatory function prior to and immediately after pPCI, on the 1st, 3rd, and 5th day of the index hospitalization using novel CMR techniques, (ii) assessment of glucose and lipid metabolism, and (iii) readouts of various organ and tissue functions during and after STEMI, including the liver, the pancreas, the spleen, and circulating blood and immune cells arising from bone marrow, the kidney, skeletal muscle, and adipose tissue. This is complemented by targeted multiomics analysis, including proteomics, lipidomics, and long-read sequencing, and novel CMR-based techniques to study myocardial flux rates and energy metabolism in mice and patients. In perspective, SYSTEMI seeks to link regional functional and structural alterations with local myocardial metabolism. Several technical improvements in recent years have facilitated the application of MRS, ^1^ H- and ^31^P-MRS measurements by reducing the scan time or voxel size for examining metabolism in infarcted and remote zones [19]. In experimental models of myocardial ischemia, substrate selection is characterized by a “metabolic switch” in myocardial energy supply from predominantly aerobic FA oxidation to anaerobic glycolysis. ^1^ H-MRS may estimate myocardial triglyceride and total creatine levels, whereas ^31^P-MRS is able to quantify metabolites such as phosphocreatine, ATP, their ratio or creatine kinase fluxes [26]. Currently, data are lacking for CMR/MRS measurements that comprehensively characterize metabolic alterations in ischemic and remote myocardium with respect to coronary artery disease severity using ^1^ H- and ^31^P-MRS. In perspective, myocardial metabolism will be further assessed by use of hyperpolarized ^13^ C-substrates, such as pyruvate, bicarbonate or lactate, combined with advanced deuterium metabolic imaging [27].

## Conclusion

SYSTEMI aims to identify individuals with distinct susceptibility to myocardial ischemia among the different endotypes of T2DM across the glucometabolic spectrum, endotypes of anemia and lipid disorders, paving the way for precision medicine in STEMI and cardiometabolic disorders.

## Data Availability

The datasets generated during and analyzed during the current study are not publicly available due to the fact that the trial is still recruiting and preliminary results not published in peer reviewed journals but are available from the corresponding author on reasonable request.

## Abbreviations

AI: Artificial intelligence
CEST: Chemical exchange saturation transfer
CS: Cardiogenic shock
CKD: Chronic kidney disease
CMR: Cardiac magnetic resonance
CRC: Collaborative Research Consortium
DMC: Data Monitoring Committee
DOSAR: Düsseldorf outcome and safety registry
EAC: Endpoint Adjunction Committee
EF: Ejection fraction
ECV: Extracellular volume fraction
EDV: End-diastolic volume
ESV: End-systolic volume
FMD: Flow-mediated dilatation
FU: Follow-up
HbA1c: Hemoglobin A1c
HOMA: Homeostasis model assessment
IMH: Intramyocardial hemorrhage
ID: Iron deficiency
IS: Infarct size
LAS: Large artery stiffness
LDL-C: Low-density lipoprotein cholesterol
LV: Left ventricle
MACEs: Major adverse cardiovascular events
MRS: Magnetic resonance spectroscopy
MVO: Microvascular obstruction
6MWT: 6 min walk test
NAFLD: Non-alcoholic fatty liver disease
OGTT: Oral glucose tolerance test
pPCI: Primary percutaneous coronary intervention
PWV: Pulse wave velocity
SIRD: Severe insulin-resistant diabetes
SMuRF: Standard modifiable cardiovascular risk factor
SOP: Standard operating procedure
STEMI: ST-segment elevation myocardial infarction
SV: Stroke volume
SYSTEMI: Systemic organ communication in STEMI
TMC: Trial Management Committee
T2DM: Type 2 diabetes mellitus
